### Cluster selection

We will define a cluster as a BRAC PO area, which will consist of a pair of BRAC village field workers (called Shasthya Kormi or SK) and their 20 BRAC village volunteers (referred to as Shasthya Shebika or SS) who are supervised by a single BRAC PO. A BRAC PO area approximately comprises of 40 to 50 villages with an average population of 13,000 people. We will have a total number of 112 BRAC PO for randomisation. We will randomly select 100 clusters with an equal number of clusters in each arm. The research team took written approval for the study from Directorate General of Health Service (DGHS) under Ministry of Health & Family Welfare before allocating the clusters to a treatment group or the trial interventions begin.

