### Eligibility criteria for inclusion of cluster

We will exclude any potential BRAC PO area (cluster) if there are any other maternal and or neonatal interventions either by the government or non-government organisations in the area. We will identify any such program by contacting local officials in the sub-districts in the Dhaka Division. We will exclude areas where access is extremely difficult, for example in flood-prone areas. All women aged between 15 to 49 years, who are pregnant and their gestational age is ≤90 days, and are permanent residents of the Shonjibon study area will be eligible for the study.

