### Sampling frame and sample size

To detect a 25% reduction in neonatal mortality (33 neonatal deaths/1000 live births in control to 24.8 neonatal deaths/1000 live births in the intervention group), with 90% power, 5% two-sided alpha, 1:1 ratio of treatment allocation and intra-cluster correlation coefficient (ICC) of 0.0245, we require 100 clusters (each covering an average of 4000 households), or 50 clusters per treatment group, with a total of 30,000 live births over one year. This sample would allow detection of a 22% relative difference between treatment groups with 80% power. To detect a 30% reduction in preterm delivery from 15% in control compared to 10.5% in the intervention arm, assuming 80% power, 5% level of significance, intracluster correlation of 0.012 for small birth size (Bangladesh DHS data), would require a sample size of 1300/arm or 40 pregnant women from 64 clusters. A smaller sample size of 570 women/arm or 40 pregnant women from 28 clusters is needed to detect a 30% reduction in LBW with the same assumptions. Our cluster is one BRAC PO area that consists of ~ 13,000 people. Assuming a crude birth rate of 23 per 1000 people, 10% loss of pregnancies before birth and 15% loss to follow up each cluster will yield 300 births over 15 months, and this will be sufficient to reach the desired sample size.

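### The sample-size section gives two accrual periods for the same 30,000 live births; one year fails on any reading that applies the 15% loss, and 15 months suffices only if the 10% pregnancy loss is not deducted

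*Protocol article*

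**What the plan says.** All the figures are in the protocol article, mostly under Sampling frame and sample size.

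- **Requirement.** 100 clusters, 50 per arm, "with a total of 30,000 live births over one year". That is 300 live births per cluster in 12 months.
- **Yield.** "Our cluster is one BRAC PO area that consists of ~ 13,000 people"; the Cluster selection section agrees ("with an average population of 13,000 people"). The calculation then runs: "Assuming a crude birth rate of 23 per 1000 people", followed by "10% loss of pregnancies before birth and 15% loss to follow up each cluster will yield 300 births over 15 months". The paragraph concludes that this is enough to reach the desired sample size.
- **Who can be enrolled.** The eligibility section admits women "who are pregnant and their gestational age is ≤90 days". The Recruitment and consent section registers a woman only if the pregnancy test is positive in the first trimester, and asks for written consent.

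**The concern.** The opening and closing sentences of one paragraph describe the same 300 births per cluster but allow 12 months in one place and 15 in the other. Only one can be the plan.

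The closing sentence also names its inputs, so it can be checked, and its output does not follow from them. The yield starts from all births in the population and deducts only pregnancy loss and loss to follow-up. It has no visible term for pregnancies found after 90 days or for women who decline.

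At stake is whether the claim of sufficiency holds, and how long field teams, supplies and budget must run. A trial planned on one year would stop well short of its required size.

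**Working it through.** **Inputs (Sampling frame and sample size):** population per cluster 13,000; crude birth rate 23 per 1000, taken as annual; pregnancy loss 10%; loss to follow-up 15%; 100 clusters; target 300 per cluster.

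**Formula:** births per cluster = population × birth rate × (months/12) × (1 − each loss).

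**Base, no losses:** 13,000 × 0.023 = 299 in a year; × 1.25 = 373.75 in 15 months.

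**Trying to reproduce 300:**

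| Losses applied | 12 months | 15 months |
|---|---|---|
| Both, multiplied (0.90 × 0.85 = 0.765) | 228.7 | 285.9 |
| Both, added (0.75) | 224.3 | 280.3 |
| Follow-up loss only (0.85) | 254.2 | 317.7 |
| Pregnancy loss only (0.90) | 269.1 | 336.4 |
| None | 299.0 | 373.8 |

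Only two routes come within 3% of 300. One is 12 months with neither stated loss (299). The other divides by 1.10 and 1.15 over 15 months: 373.75 / 1.265 = 295.5. The first discards both losses that the sentence names; the second is not how a percentage loss is applied.

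**Totals over 100 clusters:**
- Both losses: 22,874 in a year (23.8% below 30,000); 28,592 in 15 months (4.7% below).
- Follow-up loss only: 25,415 in a year (15.3% below); 31,769 in 15 months (5.9% above).

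**Time to reach 300 per cluster:**
- Both losses: 300 / 228.7 × 12 = 15.7 months.
- Follow-up loss only: 300 / 254.2 × 12 = 14.2 months.

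**Room for late detection and refusal at 15 months:** with follow-up loss only, 300 / 317.7 = 0.944, so about 94% of pregnancies must be enrolled by 90 days with consent. With both losses there is no room, because the yield is already below 300.

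**Effect on power.** Let m be births per cluster. The design effect is 1 + (m − 1) × ICC and the effective size per arm is 50m divided by it. The test compares 33/1000 with 24.8/1000 at two-sided 5%. The protocol prints an ICC of 0.0245. At m = 300 that gives a design effect of 8.3 and power of about 31%, not the stated 90%. An ICC of 0.00245 gives a design effect of 1 + 299 × 0.00245 = 1.733, an effective 15,000 / 1.733 = 8,658 or so per arm, and power of 89.6%. It also gives 80.8% for the 22% reduction quoted at 80% power. I use 0.00245 below as an assumption, because it reproduces the plan's own power.

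| Births per cluster | Source | Power, ICC 0.00245 (assumed) |
|---|---|---|
| 300 | target | 89.6% |
| 285.9 | 15 months, both losses | 88.8% |
| 254.2 | one year, follow-up loss only | 86.6% |
| 228.7 | one year, both losses | 84.3% |

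At the printed 0.0245, power is between 30% and 31% at all four sizes, so accrual hardly matters there. The ICC discrepancy is a separate matter.

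**The case against.** The strongest reply is that the 15-month plan may be sound. A crude birth rate counts births, so pregnancies lost before birth are already excluded from it, and deducting 10% again counts that loss twice. Without the deduction, 15 months gives 318 per cluster, above target. Even with it, the gap is 4.7% on a population given only approximately; about 13,640 people per cluster would close it (300 / (0.023 × 1.25 × 0.765)), and under one point of power is lost. This stands. A reader might infer that 30,000 births cannot be delivered, but at 15 months the documents do not support that. The reply does not rescue the one-year phrase, which gives at most 254 per cluster once the 15% is applied.

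A reader might also infer a large loss from the 90-day limit, pointing to the median start of antenatal care at 5.2 months. That figure describes women seeking care under usual programmes. The trial finds pregnancies through door-to-door visits and menstrual tracking, with incentives for early identification by the village volunteers in intervention clusters and similar detection methods in control clusters. The documents give no capture rate, so any specific shortfall or power loss from this source would be guesswork.

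Finally, a condensed article may leave a recruitment fraction to the full protocol. Its absence alone is not an error. It matters here only because the article asserts sufficiency and the margin behind that assertion is at most about 6%.

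**Conclusion.** The point holds in a limited form. The paragraph contradicts itself on accrual time, and its yield of 300 in 15 months does not follow from its own inputs. One year falls short by 15% to 24% depending on whether the 10% is deducted. Fifteen months falls 4.7% short if it is deducted and exceeds the target by 5.9% if it is not; in the second case enrolment by 90 days with consent must reach about 94%.

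The conclusion rests on the birth rate being annual, on 13,000 people per cluster, and on the 15% loss being applied as stated. The consequence for power is small at 15 months and moderate at one year (about 3 to 5 points), conditional on the assumed ICC of 0.00245. This is a planning figure to correct; it does not threaten the design.

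**What to change.** 1. Keep 30,000 live births as the required size. It comes from the power calculation and should not be lowered to match a projected yield.
2. Delete the one-year phrase and state one accrual period, with the arithmetic shown: about 15.7 months for 300 per cluster if both losses apply, about 14.2 months if the 10% does not.
3. Say what the 10% applies to: enrolled pregnancies, or the birth-rate figure itself.
4. State the fraction of pregnancies assumed to be enrolled by 90 days with consent, and lengthen the accrual period to match if that fraction leaves the yield below 300.

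The cost is a few rewritten sentences. If the literal reading of both losses is intended, accrual also runs about three weeks beyond 15 months.

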### Recruitment and consent of women

In the intervention clusters, SSs will make systematic door-to-door visits to identify new pregnancies through menstrual cycle tracking of all women of reproductive age. Once the woman reports a missed period, the SS will immediately notify the Field Implementers by mobile phone. The Field Implementers will then visit the pregnant mother along with the SS within the next 48 h to conduct a pregnancy test and enquire about the last menstrual period. If the pregnancy test is positive and the pregnancy is within the first trimester, the Field Implementers will register the mother and seek written consent. We will obtain written, witnessed informed consent from all participants.

### Assignment of treatments

An investigator remote from the field area will assign the interventions to eligible clusters using a fixed randomisation scheme with a uniform allocation ratio of treatments, stratified by subdistrict or Upazila. The random allocation sequence will be generated using Stata 12 software (StataCorp. 2011. Stata Statistical Software: Release 12. College Station, TX: StataCorp LP). The nature of the intervention precludes the masking of the treatments.

### Evaluation

#### Data collection team

A separate team of trained data collectors not involved in the implementation of the intervention will collect data for evaluation. The evaluation team will consist of 135 data collectors, five field supervisors and five field research officers. Each data collector will be responsible for one cluster. We will train the evaluation team over a four-week period, and standardize measurement methods and retrain as needed every six months.

#### Data collection schedule

The data collectors will visit each woman a total number of six times from the time of enrolment till 42 days after delivery. These visits will be made between 12 and 14 weeks, 20–24 weeks, 28–32 weeks, within 24 h of delivery, 7–10 days after delivery, 38–42 days after delivery (Fig. 2).

**Fig. 2 Fig2:**
[figure not shown]
Trial flow chart and intervention schedule

#### Types of information collected

Over the pregnancy and neonatal period, data collectors will collect information regarding household characteristics, reproductive history, pregnancy information, medication history, details about consumption of IFA supplements, current health status, any side effects from the supplements, antenatal care, birth outcome, birth weight, immediate newborn care and neonatal deaths. We will also collect information on exposure to household air pollution and out of pocket expenses for any antenatal and postnatal care seeking (Table 1).

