IFA supplements have also been found to reduce the preterm delivery rate and neonatal mortality attributable to prematurity and birth asphyxia [7]. Other studies from low-income countries have reported that preterm delivery is one of the main contributors to neonatal deaths [12, 13]. These results combined indicate that IFA supplements in populations of iron-deficient pregnant women could lead to a decrease in the number of neonatal deaths mediated by reduced rates of preterm delivery. We thus propose a large-scale prospective trial to measure the impact of the early introduction of antenatal iron/folic acid supplementation in pregnancy on neonatal outcomes in rural Bangladesh. We will employ a community-based, cluster randomized controlled trial design, in which pregnant women will be randomly allocated to the enhanced iron/folic acid distribution program, or to the current usual programs. We have chosen the current usual programs as our comparator. We didn’t consider placebo because WHO and Government of Bangladesh have a recommendation that pregnant women should receive 60 mg of iron supplementation. But the implementation of this recommendation is inadequate. Surveys indicate that only 52% of rural women reported any use of iron/folic acid in their last pregnancy but this dropped to 39% for the poorest households, and to 34% for women with no education (3). Also, the median gestation when women start antenatal care (and would have access to iron/folic acid supplements) is 5.2 months (3) .

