### Objectives and hypothesis

The trial objectives are to evaluate the effect of early availability and promotion of IFA supplements on neonatal mortality, low birthweight and preterm delivery. The primary hypothesis is that in a community-based, cluster randomized controlled trial of women from rural Bangladesh, daily supplementation with 60 mg elemental iron and 400 μg folic acid starting in the first trimester of pregnancy, and sustained for at least 180 days, will reduce neonatal mortality by 25% from 33/1000 to 24.8/1000 live births compared to usual iron-folic acid supplementation programs.

The secondary hypotheses are that the early availability and promotion of IFA supplements in intervention clusters will reduce preterm delivery by 30% (15% in control to 10.5% in intervention), and low birth weight by 30% (15% in control to 10.5% in intervention). We further hypothesised that household wealth and maternal education would modify the neonatal mortality responses with a greater reduction for women from the poorest households, and women with no education. We also hypothesised that the early start to IFA supplements would not increase iron-related side effects, e.g. nausea & vomiting in intervention clusters and will be cost-effective in reducing neonatal mortality in intervention clusters.

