#### Trial outcomes

The primary trial outcome will be the difference in the neonatal mortality rate between the intervention and control areas. The secondary trial outcomes will include: (1) percentage of women using IFA supplements in the first trimester of pregnancy; (2) percentage of live births with low birth weight and with preterm delivery; (3) percentage of neonatal deaths attributable to preterm delivery, and to birth asphyxia; (4) mean marginal additional expenditure associated with early IFA supplements, and the mean cost per neonatal death prevented; (5) the percentage of pregnant women reporting side effects including nausea and vomiting.

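### The listed side-effect item is tied to the supplements, while the hypothesis and outcome compare all pregnant women by arm; used as the outcome source, it would over-count symptoms in the intervention arm

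*Protocol article*

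**What the plan says.** Three sections of the protocol article bear on tolerability.

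- **Objectives and hypothesis** makes a between-arm claim: "We also hypothesised that the early start to IFA supplements would not increase iron-related side effects, e.g. nausea & vomiting in intervention clusters".
- **Trial outcomes** lists as the fifth secondary outcome "the percentage of pregnant women reporting side effects including nausea and vomiting". The denominator is pregnant women, and nothing links the symptom to a tablet.
- **Types of information collected** gives the items: "details about consumption of IFA supplements, current health status, any side effects from the supplements, antenatal care, birth outcome". Side effects are tied to the supplements. A current-health item is listed separately, and its content is not described.

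Collection runs throughout: "Over the pregnancy and neonatal period, data collectors will collect information regarding household characteristics". On the antenatal visits, Data collection schedule says: "These visits will be made between 12 and 14 weeks, 20–24 weeks, 28–32 weeks".

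Uptake differs between arms by design. Women enter if they are women "who are pregnant and their gestational age is ≤90 days", and those in intervention clusters receive capsules once they consent (Regular supply of IFA supplements and counselling). Control women have the usual programme with no added counselling (Control). For usual care, the Background reports 52% of rural women with any use in the last pregnancy, and says that "the median gestation when women start antenatal care (and would have access to iron/folic acid supplements) is 5.2 months". Assignment of treatments states that masking is not possible.

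**The concern.** The hypothesis and the outcome ask whether women offered early IFA have more nausea and vomiting than women under usual care. The listed item asks something narrower: whether a woman has had an effect that she puts down to the supplement. Only users can say yes, and the trial exists to make users more numerous and earlier in one arm.

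Nausea and vomiting also occur in pregnancy without iron. Suppose two women have the same nausea, one taking capsules and one not. The first may be counted and the second cannot be. A comparison built on this item mixes any real effect of iron with the difference in who takes tablets.

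This is the only tolerability outcome that the article states. A spurious increase would count against the trial's own hypothesis and could discourage early supplementation. An analysis plan could not repair it later, because symptoms that non-users were never asked about cannot be recovered.

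**Working it through.** The article gives no expected side-effect rate, so there is no stated figure to reproduce. The check asks what the listed item would show if IFA caused no symptoms at all.

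**Formula.** Recorded rate in an arm = u × s × a, where
- u = share of women using IFA,
- s = share with the symptom (equal in both arms under no true effect),
- a = share of users with the symptom who attribute it to the tablet.

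If s and a are equal in both arms they cancel, and the ratio of recorded rates is u(intervention) / u(control).

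**Inputs from the article**
- Control, any use in pregnancy: 52% (Background, rural survey). An alternative is 40% (Discussion, baseline of an earlier home-care trial in rural Bangladesh).
- Intervention, any use in pregnancy: 84% (Discussion, home-care arm of that earlier trial). This is a proxy, since the article gives no expected uptake for this trial.

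**Assumed inputs.** s and a are not in the article and are varied below.

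**Whole pregnancy**
- Ratio: 0.84 / 0.52 = 1.62. With 40% control use: 0.84 / 0.40 = 2.10.

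| s | a | Intervention (84%) | Control (52%) | Difference |
|---|---|---|---|---|
| 30% | 30% | 7.6% | 4.7% | 2.9 points |
| 50% | 50% | 21.0% | 13.0% | 8.0 points |
| 70% | 50% | 29.4% | 18.2% | 11.2 points |

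Middle row: 0.84 × 0.5 × 0.5 = 0.21 and 0.52 × 0.5 × 0.5 = 0.13.

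**Would the artefact be noticed?** The planned size is 30,000 live births, or 15,000 per arm and about 300 per cluster. The design effect is 1 + 299 × ICC. No intracluster correlation is given for side effects, so two values are tried.
- ICC 0.012 (the article's value for small birth size): design effect 4.59, effective size 15,000 / 4.59 ≈ 3,270 per arm. The chance of a significant difference (two-sided 5%) is above 99% in all three rows.
- ICC 0.05 (assumed): design effect 15.95, effective size ≈ 940 per arm. The chance is 74%, above 99% and about 100% in the three rows.

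**The 12–14 week visit.** The entry limit of 90 days is 90 / 7 = 12.9 weeks, so intervention women will have been given capsules by about this visit. The usual-care median of 5.2 months is about 5.2 × 30.4 / 7 = 22.6 weeks, which falls in the 20–24 week window. The uptake gap is therefore probably widest at the first visit. Uptake by arm at that time is not stated. As pure assumptions, 90% against 20%, 10% or 5% would give ratios of 4.5, 9 and 18.

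**Unequal attribution.** If a differs by arm, the ratio becomes (0.84 / 0.52) × a(intervention) / a(control). It returns to 1 only if users in the intervention arm attribute symptoms 0.52 / 0.84 = 0.62 times as readily as control users. Fortnightly visits and compliance calls could raise or lower attribution, and the article does not say which.

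**With a common, unattributed list** the recorded rate is s in each arm. Under no true effect the ratio is 1 and the difference 0, apart from any reporting bias due to lack of masking.

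**The case against.** The strongest reply is that a one-sentence list of topics is being read as an outcome definition. Trial outcomes counts pregnant women reporting side effects and does not mention attribution. The questionnaire and the assessment table are not shown, and a journal article commonly leaves item wording to fuller documents. The separate current-health item could already record nausea and vomiting in both arms.

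This stands as a limit on certainty. The article does not show that the objective is unanswerable, only that the one side-effect item it names does not match the outcome. It does not remove the point, because nothing in the article links the current-health item to this outcome.

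The usual-care figures also come from general surveys. Control women here are identified by similar methods and receive BRAC antenatal care, so their uptake could be higher or earlier than 52% and 5.2 months suggest. That would shrink the ratio. It would reach 1 only if uptake were equal, which would defeat the trial's purpose.

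A reader might infer four stronger things, none of which the article supports:
- **That symptoms would be counted in the intervention arm only.** Control users can report too; the middle case gives them 13%.
- **That measurement is confined to the first trimester.** There are three antenatal visits, and the later ones fall when control women may be taking IFA.
- **That 84% can stand for uptake by 14 weeks.** It is use at any time, and the Discussion says those women did not begin early.
- **That a superiority design without a margin cannot support the hypothesis.** The superiority label describes the trial as a whole. No section says that a non-significant result will be read as proof, and a margin for a secondary outcome may sit in the analysis plan.

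**Conclusion.** The point holds as a mismatch with a predictable direction. The hypothesis and the outcome concern all pregnant women in both arms, while the only side-effect item listed can be reported by supplement users alone. If the outcome is built from that item, the comparison is biased against the intervention even when IFA has no effect on symptoms.

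The spurious ratio is about 1.6 over the whole pregnancy, or 2.1 with the lower control figure. It is probably larger at the first visit, by an amount that the article does not allow one to fix. The ratio rests on the 84% proxy, the survey figures for usual care, and equal symptom and attribution rates in users. The absolute gap of about 3 to 11 points rests also on assumed nausea and attribution rates and is illustrative.

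The conclusion is conditional on the source of the outcome. It falls away if the current-health item already puts the same symptom questions to every woman and feeds the fifth secondary outcome.

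**What to change.** Reconcile Objectives and hypothesis, Trial outcomes and Types of information collected.

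1. At the 12–14, 20–24 and 28–32 week visits, ask every woman in both arms the same symptom list, including nausea and vomiting, whatever her IFA use and without asking for a cause. If the current-health item already does this, name it as the source of the fifth secondary outcome.
2. Define the outcome as the percentage of all women with each symptom, and compare arms with a cluster-adjusted 95% confidence interval.
3. Keep effects that women attribute to the supplement as description only, not as a between-arm comparison.

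The cost is a reworded item in the tablet application and a sentence in the outcome definition. The visits and the separate evaluation team are already planned. Recorded symptom rates will be higher in both arms, because ordinary pregnancy symptoms are then counted for everyone. Unmasked reporting may still leave some bias, which the report should acknowledge.
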